### Study Population

Patients aged between 35 and 75 years scheduled for primary cataract surgery by phacoemulsification, in whom intraoperative posterior capsular rupture or deficient zonular support precludes in-the-bag IOL implantation, will be considered for inclusion. Inadequate posterior capsular support was defined as one or more of the following intraoperative conditions: posterior capsular rupture with vitreous disturbance, zonular dialysis exceeding 3 clock hours, or combined zonular-capsular instability preventing safe in-the-bag fixation. All surgeons will follow this standardized definition to ensure uniform eligibility.

### Eligibility Criteria

Inclusion and exclusion criteria for study participation are summarized in Textbox 1 (see Multimedia Appendix 1 for the sample size calculation).

Textbox 1.Inclusion and exclusion criteria of the study population.
**Inclusion Criteria**
Patients aged 35 to 75 years undergoing primary cataract surgery by phacoemulsificationPresence of inadequate posterior capsular support identified intraoperatively, including posterior capsular rupture with vitreous disturbance or zonular dialysis exceeding 3 clock hoursInability to safely implant an in-the-bag IOL due to capsular or zonular instabilityBoth male and female patientsWillingness to provide written informed consentAbility and willingness to comply with postoperative follow-up schedule
**Exclusion Criteria**
Pre-existing corneal diseases such as keratitis, corneal dystrophy, or corneal opacitiesHistory of chronic or recurrent uveitisAdvanced glaucoma (intraocular pressure greater than 21 mm Hg despite medication or optic nerve cup-to-disc ratio greater than 0.7)Retinal pathologies, including diabetic retinopathy, hypertensive retinopathy, age-related macular degeneration, or retinitis pigmentosaTraumatic aphakia or lens subluxation secondary to ocular traumaActive ocular infection or uncontrolled systemic disease likely to impair wound healing

### Randomization, Allocation Concealment, and Blinding

Eligible patients will be randomly allocated in a 1:1 ratio into 2 groups: group A (retropupillary iris-claw IOL) and group B (scleral-sutured fixation). A computer-generated block randomization sequence (block size of 4) will be prepared by an independent statistician. The group assignment will be concealed in sequentially numbered, opaque, sealed envelopes opened only after capsular deficiency confirmation during surgery.

Due to the nature of the interventions, blinding of surgeons and patients will not be feasible. However, postoperative outcome assessors and data analysts will remain blinded to the intervention group to minimize observer bias. Postoperative assessors will follow standardized grading protocols and will remain masked to group assignment to reduce detection bias.

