**Methods:**

This is a prospective, 2-arm, open-label randomized controlled trial being conducted at the Department of Ophthalmology, Acharya Vinoba Bhave Rural Hospital, Sawangi, India. A total of 92 patients aged 35 to 75 years with intraoperative posterior capsular compromise will be randomized (block randomization, sealed opaque envelopes) into 2 groups: group A (retropupillary iris-claw IOL) and group B (scleral-sutured IOL). Preoperative, intraoperative, and postoperative data will be collected at day 1, day 15, day 30, and day 90. The primary outcomes are best-corrected visual acuity and lens-induced astigmatism at 3 months. Secondary outcomes include IOL centration or tilt, intraoperative and postoperative complications, and patient satisfaction (assessed using the National Eye Institute Visual Function Questionnaire-25). Data will be analyzed using ANOVA and mixed-effects models.

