### Study Setting

All surgical and postoperative procedures will be performed in the dedicated ophthalmic operation theaters of AVBRH under standardized aseptic conditions by trained consultant ophthalmic surgeons. Each participating surgeon will have independently performed at least 30 cases of both iris-claw and scleral-sutured IOL fixation techniques to ensure procedural consistency.

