This trial’s methodological design addresses previous limitations by incorporating randomization, allocation concealment, and masked outcome assessment. Objective parameters such as IOL tilt and decentration will be evaluated using slit-lamp retroillumination and validated anterior-segment optical coherence tomography methods described by Calzetti et al [10], ensuring quantitative reproducibility. In addition, the inclusion of patient-reported outcomes using the National Eye Institute Visual Function Questionnaire-25 will provide valuable insights into subjective satisfaction and functional vision, which have often been underrepresented in earlier studies.

Ethical oversight, AE monitoring, and quarterly data review by an independent committee have been included to maintain methodological rigor and compliance with Good Clinical Practice guidelines. The statistical plan using mixed-effects modeling and repeated-measures ANOVA will allow robust analysis of longitudinal data while accounting for missing values. The trial does not include an economic analysis, as cost-effectiveness was beyond the scope of the present protocol; however, results regarding operative time and complication rates may have indirect implications for resource optimization in tertiary-care settings. Potential limitations of this study include its single-center design and limited sample size, which may influence external generalizability. Nonetheless, the use of standardized surgical techniques, strict eligibility criteria, and a uniform postoperative evaluation schedule are expected to enhance internal validity and reproducibility.

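### A single fixed block size of 4, with unblinded surgeons at one centre, lets on average up to one third of allocations be foreseen by anyone who knows the earlier ones

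*Protocol article*

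**What the plan says.** The section Randomization, Allocation Concealment, and Blinding sets the ratio ("Eligible patients will be randomly allocated in a 1:1 ratio into 2 groups") and the method ("A computer-generated block randomization sequence (block size of 4) will be prepared by an independent statistician"). It names one block size only, with no varying sizes and no stratification. Concealment is by "sequentially numbered, opaque, sealed envelopes opened only after capsular deficiency confirmation during surgery". The same section says that "blinding of surgeons and patients will not be feasible", while outcome assessors and analysts are masked.

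The Abstract gives the size: "A total of 92 patients aged 35 to 75 years with intraoperative posterior capsular compromise will be randomized". The Discussion confirms one centre: "Potential limitations of this study include its single-center design and limited sample size". Study Setting has the operations done "by trained consultant ophthalmic surgeons"; there is more than one surgeon, but the number is not given.

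Study Population defines inadequate support by three intraoperative conditions: capsular rupture with disturbed vitreous, zonular dialysis beyond 3 clock hours, or combined instability that rules out safe fixation in the bag. It adds: "All surgeons will follow this standardized definition to ensure uniform eligibility". Textbox 1 also requires that in-the-bag implantation cannot be done safely. Results says that enrolment was still under way when the article was submitted.

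**The concern.** With a fixed block of 4 at 1:1, the last allocation in every block follows from the first three, and the third follows from the first two when those agree. A sealed envelope hides its own contents but not what can be inferred from envelopes already opened. Surgeons see the arm once it is assigned, all patients come from one department, and the envelopes are numbered in sequence. If there is one list starting at 1, numbers 4, 8, 12 and so on close a block, so the number shows the position.

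Entry is decided in theatre by an unblinded operator. Two of the three conditions are largely observable signs. The combined-instability condition and the safety requirement in Textbox 1 are judgments without a threshold. A surgeon who expects a particular arm could therefore enter or withhold a borderline eye. There is a possible motive: Hypothesis expects the iris-claw technique to be quicker with fewer complications, and the Introduction and Discussion describe scleral suturing as more demanding.

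The stake is comparability of the arms in capsular damage, which could affect complications, centration and vision. Data Management and Statistical Analysis names age and preoperative vision as the adjustment covariates, so steering on intraoperative severity would remain. Masked assessors protect against detection bias, not against selection at entry.

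**Working it through.** The article states no predictability figure, so there is none to reproduce.

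**Inputs from the article.** Block size 4; ratio 1:1, hence 2 A and 2 B per block; N = 92, hence 92/4 = 23 complete blocks and exactly 46/46.

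**Step 1: allocations that are certain with full knowledge.** Assume that the observer knows the block size, the block boundaries and every earlier allocation. An allocation is certain once one arm is used up in the block.

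| Block | Certain positions | Count |
|---|---|---|
| AABB, BBAA | 3 and 4 | 2 each |
| ABAB, ABBA, BAAB, BABA | 4 | 1 each |

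Mean per block = (2×2 + 4×1)/6 = 8/6 = 1.333. Share = 1.333/4 = 33.3%. Over the trial, 23 × 1.333 = 30.7 of 92. The possible range is 23 (one per block) to 46 (two per block).

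**Step 2: best guess with full knowledge.** The observer always names the arm with more places left.
- Position 1: 1/2.
- Position 2: 2/3.
- Position 3: the first two agree with probability 1/3 (certain) and differ with probability 2/3 (even odds), so 1/3 + 2/3 × 1/2 = 2/3.
- Position 4: 1.

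Mean = (0.500 + 0.667 + 0.667 + 1.000)/4 = 70.8%, against 50% by chance.

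**Step 3: partial knowledge.** Assume that each earlier allocation is known independently with probability q and that block boundaries are known. At position 4, certainty needs both members of the used-up arm to have been seen: q². At position 3 it needs the first two to agree and both to have been seen: q²/3. Per block this is q² + q²/3 = 4q²/3; divided by 4, the share is q²/3. A simulation agreed.

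| q (assumed) | Certain share | Of 92 |
|---|---|---|
| 1 | 33% | 30.7 |
| 0.75 | 19% | 17.3 |
| 0.5 | 8% | 7.7 |
| 1/3 | 4% | 3.4 |

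**Step 4: other block schemes.** Fixed sizes were enumerated. Random sizes were simulated over 92 patients, with an observer who knows all earlier allocations and the possible sizes but not their order.

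| Scheme | Certain | Best guess right |
|---|---|---|
| Fixed 4 | 33.3% | 70.8% |
| Fixed 6 | 25% | 68.3% |
| Fixed 8 | 20% | 66.6% |
| Random 4, 6 | about 5.5% | about 69% |
| Random 4, 6, 8 | about 2% | about 68% |

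Varying the size removes nearly all certainty but leaves most of the guessing advantage.

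**The case against.** The strongest reply is that one third is the full-knowledge case. Several surgeons share the list, and nothing in the article says that each of them learns the others' allocations or tracks block boundaries. A surgeon with partial knowledge can predict far less, as step 3 shows. This stands, and the figure must be given with its assumption and range. Nothing in the article prevents shared knowledge within one department, however, so the full-knowledge case cannot be excluded either.

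Second, the article has real safeguards: a common definition with two largely observable conditions, envelopes opened only after the deficiency is confirmed, and quarterly committee review of recruitment and protocol compliance (Adverse Event Reporting and Monitoring). These narrow the room to act on a prediction. They do not stop the prediction, because it rests on past allocations and can be made before the surgeon declares the deficiency confirmed.

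Third, a condensed article may leave envelope custody, screening logs and what surgeons are told to the full protocol. That is fair, and none of those is counted as a fault here. The single block size is different: it is a stated choice.

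A reader might infer that a third of allocations were in fact known to surgeons, or that selection bias has occurred. The article supports neither. It does not report what surgeons knew, and it gives no data on entry decisions.

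**Conclusion.** The point holds as an avoidable risk of selection bias in a stated design choice. Under full knowledge of earlier allocations and block boundaries, on average 33.3% of allocations (30.7 of 92) are certain beforehand and a best guess succeeds 70.8% of the time. Under partial knowledge the certain share is q²/3, for example 19% at q = 0.75 and 8% at q = 0.5. The value of q is an assumption; the documents do not give it. The effect on visual acuity or astigmatism cannot be estimated from the article, because it depends on how many eyes are borderline and whether surgeons act on a prediction. The change is a cheap improvement; its absence does not invalidate the trial.

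**What to change.** For envelopes not yet used, starting at the next block boundary, have the independent statistician regenerate the list with randomly varying block sizes, for example 4, 6 and 8, and keep the sizes and their order from surgeons and theatre staff. Report the change and the envelope number at which it took effect. Eligibility, surgery, outcomes and sample size stay as they are.

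**Gain.** Certain allocations fall to about 2% for the patients affected. Best-guess accuracy falls only to about 68%, so the change should not be presented as removing predictability.

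**Cost.** A new list and re-stuffed envelopes, and loss of the guaranteed 46/46 split. If recruitment stops inside a block of 8, the final imbalance can reach 4. If the switch is made mid-block, an abandoned block of 4 can add 2, giving up to 6, which is why the switch belongs at a block boundary.

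**Limit.** The gain applies only to patients not yet randomized. Results expects recruitment to finish in September 2025, so few or none may remain. In that case the trial report should give the block size and the concealment procedure, and name this risk among the limitations.

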### Intervention Procedures

Both procedures will be performed under peribulbar anesthesia using a standardized phacoemulsification technique.

For group A, a retropupillary iris-claw IOL will be implanted using standard enclavation of haptics onto the posterior iris surface after thorough anterior vitrectomy. For group B, a single-piece foldable IOL will be fixated with 10‐0 polypropylene (Prolene) sutures passed through partial-thickness scleral flaps created at the 3- and 9-o’clock positions, ensuring equal centration. All surgeries will adhere to uniform intraoperative and postoperative protocols, including the use of balanced salt solution, intracameral antibiotics, and a topical steroid–antibiotic combination therapy postsurgery. To ensure reproducibility, procedural videos will be periodically reviewed by the data monitoring committee for intersurgeon standardization.

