### Outcome Measures

Primary outcomes:

BCVA at 3 months using Snellen’s chart, converted to logMAR values for statistical analysis.Lens-induced astigmatism, measured through keratometry and autorefractometry.

Secondary outcomes:

Intraoperative complications (posterior capsular rupture extension, vitreous loss, surgical duration).Postoperative complications (hyphema, pigment dispersion, raised intraocular pressure, IOL decentration, cystoid macular edema).IOL centration and tilt, assessed by slit-lamp retroillumination following the method of Calzetti et al [10].Patient-reported satisfaction and visual function, measured using the National Eye Institute Visual Function Questionnaire-25 at 3 months.

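### Masked postoperative assessment is claimed without exception, but cannot be relied on for the secondary outcomes graded by viewing the lens and iris

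*Protocol article*

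**What the plan says.** The section on randomization, allocation concealment and blinding concedes that "blinding of surgeons and patients will not be feasible". It then states that "postoperative outcome assessors and data analysts will remain blinded to the intervention group to minimize observer bias", and adds: "Postoperative assessors will follow standardized grading protocols and will remain masked to group assignment to reduce detection bias". Neither sentence excepts any outcome. The Discussion describes the design as "incorporating randomization, allocation concealment, and masked outcome assessment" and presents this as an answer to the limitations of earlier work.

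Intervention Procedures describes two anatomically different fixations. Group A has "standard enclavation of haptics onto the posterior iris surface". In group B the lens is held by polypropylene sutures "passed through partial-thickness scleral flaps created at the" 3- and 9-o'clock positions.

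The secondary outcomes include "IOL centration and tilt, assessed by slit-lamp retroillumination", and a list of postoperative complications that contains lens decentration and pigment dispersion. Table 1 schedules lens position at day 15, centration and tilt at day 30, and complications at day 90.

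**The concern.** A blanket promise of masking is only as good as the assessments it covers. Some of the listed outcomes require the examiner to inspect the structures by which the two arms differ. If the examiner can tell the arm, those outcomes will be reported as protected against detection bias when they are not.

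This matters most for the graded complications. The Hypothesis section expects fewer postoperative complications with the iris-claw lens, so an examiner who shares that expectation has a direction in which to err. For centration the stated expectation is only that the arms will be comparable, so the directional pull is weaker there, although the arm is most exposed.

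**Working it through.** There is no figure in the plan to reproduce and no formula applies. The check sets the masking statement against the procedures, the schedule and the outcome list.

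**Step 1: scope of the claim.** The two masking sentences and the Discussion cover postoperative outcome assessment as a whole.

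**Step 2: what distinguishes the arms.** Group A has enclavation on the posterior iris surface; group B has sutures and scleral flaps at two fixed positions. The Introduction names iris chafing, pupil distortion and suture degradation among the risks of the two techniques, so some sequelae may also point to the arm.

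**Step 3: each outcome against the view it needs.**

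| Outcome | View of lens or iris needed? | Masking |
|---|---|---|
| Lens position (day 15) | Yes; use of the slit lamp is implied | Not reliable |
| Centration and tilt (day 30) | Yes; slit-lamp retroillumination is stated | Not reliable |
| Lens decentration, as a complication | Yes | Not reliable |
| Pigment dispersion | Probably | Probably not reliable |
| Hyphema, anterior chamber reaction | Anterior segment is examined; the sign itself need not show the arm | To be settled individually |
| Cystoid macular edema | Method of detection not given | To be settled individually |
| Intraocular pressure | No, if by noncontact tonometry, which Table 1 names in the preoperative row (assumed for later visits) | Can be kept |
| Best-corrected acuity (primary) | No; Snellen chart | Can be kept |
| Lens-induced astigmatism (primary) | No; keratometry and autorefractometry | Can be kept |
| NEI VFQ-25 | Not applicable; answered by patients who are not blinded | Assessor masking gives no protection |

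**Step 4: the safeguard offered.** The only support given is standardized grading. That makes examiners grade alike; it does not hide which operation was done. The Discussion also mentions anterior-segment optical coherence tomography, but states no masked reader, and such images may themselves show the fixation.

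**Step 5: comparison.** The claim covers every row. The described assessments do not support it for the first four, all of which are secondary.

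**The case against.** **Visibility is inferred.** The article nowhere says that the fixation can be seen. The haptics lie behind the iris and the flaps are of partial thickness, so not every examination need reveal the arm. This stands as a limit on wording: unmasking is very likely when lens position is examined in detail, but not certain in every eye or for every sign. It does not rescue an unqualified claim, because nothing described conceals the fixation from the examiner.

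**The trial is declared open-label.** This is true, and the affected outcomes are secondary. But the article separately claims masked assessors and offers that as an improvement on earlier studies, so the claim needs to be accurate.

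**Primary acuity.** A reader might infer that the slit-lamp examiner also measures acuity at the same visit, so that the primary outcome is biased too. The documents do not support this. The article is silent on who refracts and in what order. Such detail is commonly left to a full protocol, and the plural use of assessors is compatible with separate staff. Astigmatism is measured by instruments.

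**All complications.** A reader might also treat the whole complication list as unmasked. That goes too far: raised pressure measured by noncontact tonometry needs no view of the fixation.

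**Inflated error rates.** It is tempting to quote a false-positive rate for an assumed amount of misrecording. Any such figure would rest wholly on an assumed size and direction of bias that the document does not give, so none is offered and none bears on severity.

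**Conclusion.** The concern holds in a limited form. The unqualified claim of masked assessment describes a property that the design very probably lacks for lens position, centration and tilt, lens decentration and, probably, pigment dispersion. Masking should not be relied on for these outcomes. The complication components among them are also where the hypothesis favours the iris-claw arm.

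The conclusion rests on one assumption: that a clinician examining lens and iris at the slit lamp can usually distinguish iris enclavation from sutured scleral fixation. The direction and size of any resulting bias are unknown and cannot be computed from the document. Neither primary outcome is shown to be affected. The point should be acted on because it changes what the trial may claim about detection bias and the correction is cheap; it does not threaten the primary comparison as described.

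**What to change.** 1. In the blinding section and the Discussion, limit the masking claim to measurements that need no view of the fixation: acuity, autorefraction, keratometry and noncontact tonometry.
2. Report lens position, centration and tilt, lens decentration and pigment dispersion as unmasked. State the masking status of every other complication individually, according to how it is detected, and do not label complications as a block.
3. At visits still to come, complete and record acuity, autorefraction and keratometry before the slit-lamp examination, using existing staff without access to the operative record where available.

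A separate reader of anterior-segment images could be considered as a partial remedy for lens position. It would be an added resource, and the images may still reveal the arm, so it does not replace steps 1 and 2.

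The cost: the blanket masking claim is given up and the order of tests becomes fixed. The adverse event and monitoring section requires prior ethics committee approval and a registry update for any amendment. Recruitment began in March 2025 and follow-up was under way at submission, so step 3 cannot change completed visits; for those, only the reporting can be corrected. No additional visit or device is needed, and treatment is unchanged.

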### Timeline of Assessments

The schedule of preoperative, intraoperative, and postoperative assessments is outlined in Table 1.

**Table 1. T1:** Timeline of clinical assessments and outcome measures.

Study phase	Assessment parameters
Preoperative	Visual acuity (Snellen’s chart), slit-lamp biomicroscopy, intraocular pressure (NCT^a^), fundus evaluation, and biometry (A-scan, keratometry)
Day 0 (surgery)	Type of IOL^b^ fixation, intraoperative complications, surgical duration, and intraoperative stability
Day 1	Corneal clarity, anterior chamber reaction, intraocular pressure, and early complications
Day 15	BCVA^c^, astigmatism (autorefractometry), anterior chamber reaction, and IOL position
Day 30	BCVA, lens centration/tilt (slit-lamp retroillumination as per Calzetti et al [10]), intraocular pressure, and patient comfort
Day 90	Final BCVA, lens-induced astigmatism, postoperative complications, and patient satisfaction (NEI VFQ-25^d^)

a NCT: noncontact tonometry.

b IOL: intraocular lens.

c BCVA: best-corrected visual acuity.

d NEI VFQ-25: National Eye Institute Visual Function Questionnaire-25.

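### Assessor masking is claimed for every postoperative outcome, but cannot be relied on for those graded by looking at the lens and its fixation

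*Protocol article*

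**What the plan says.** The section on randomization, allocation concealment and blinding concedes that "blinding of surgeons and patients will not be feasible". It then makes two statements about the people who measure outcomes. The first is that "postoperative outcome assessors and data analysts will remain blinded to the intervention group to minimize observer bias". The second is: "Postoperative assessors will follow standardized grading protocols and will remain masked to group assignment to reduce detection bias". Neither excepts any outcome. The Discussion says the design answers the limitations of earlier work by "incorporating randomization, allocation concealment, and masked outcome assessment".

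Intervention Procedures describes two different constructions. In group A, "a retropupillary iris-claw IOL will be implanted using standard enclavation of haptics onto the posterior iris surface". In group B, a foldable lens is held by polypropylene sutures "passed through partial-thickness scleral flaps created at" the 3 and 9 o'clock positions.

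Table 1 schedules IOL position at Day 15, and the Day 30 row includes "lens centration/tilt (slit-lamp retroillumination". Day 90 covers final BCVA, lens-induced astigmatism, postoperative complications and the NEI VFQ-25. Outcome Measures lists pigment dispersion and IOL decentration among the postoperative complications.

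**The concern.** Masking of assessors protects an outcome only if the assessment itself does not disclose the arm. Here the thing to be graded (where the lens sits, whether it is centred or tilted, whether pigment has been shed) lies next to the thing that was randomized, namely how the lens is held. Standardized grading can make judgements more uniform, but it does not hide the allocation from the grader.

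This matters because the Hypothesis section is directional for these outcomes: it expects fewer complications with the iris-claw lens and comparable centration. A grader who can tell the arm and knows the hypothesis is the situation that the masking statement is meant to exclude. A reader of the results would credit centration, tilt and the judgement-based complications with a protection that they probably lack.

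**Working it through.** The document gives no figure that bears on this point, so the check sets its statements side by side.

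1. **Scope of the claim.** Masking is asserted twice in Methods and again in the Discussion, each time for postoperative outcome assessment as a whole.

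2. **What differs between arms.** Group A has haptics fixed to the back of the iris. Group B has a different lens type, sutures, and scleral flaps at two fixed clock positions. The Introduction adds that the techniques carry distinct risks and names iris chafing, pupil distortion and suture degradation, so the findings themselves may also point to the arm.

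3. **How each outcome is obtained.**

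| Outcome | Method or timing in the article | Does grading require viewing the lens or its support? |
|---|---|---|
| IOL position | Day 15 | Yes |
| IOL centration and tilt | Slit-lamp retroillumination, Day 30 | Yes |
| IOL decentration, pigment dispersion | Listed postoperative complications; method not named | Very likely |
| Hyphema | Listed postoperative complication; method not named | Probably read in the same examination |
| Raised intraocular pressure, cystoid macular edema | Listed postoperative complications | Not by their nature |
| BCVA (primary) | Snellen chart, Days 15, 30 and 90 | No |
| Lens-induced astigmatism (primary) | Keratometry and autorefractometry | No |
| NEI VFQ-25 | Day 90, patient-reported | No grader, but the respondent is unmasked |

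4. **Is anything described that would hide the fixation?** No. The article mentions no separate image reader, no cropped images and no division between the acuity examiner and the slit-lamp examiner. The Discussion adds anterior-segment optical coherence tomography for tilt and decentration, but does not say that a masked reader grades it. Table 1 and Outcome Measures name only the slit lamp.

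5. **Does this reach the primary outcomes?** Only through a route that the article leaves open. BCVA shares the Day 15 and Day 30 visits with lens grading. It shares Day 90 with the complication assessment, which includes decentration and pigment dispersion. If one person does both, or reads the operative record first, BCVA is measured by someone who may know the arm. The article neither says that this happens nor excludes it. Unmasked patients could also tell the examiner. Masking of the data analysts is untouched by any of this.

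**The case against.** The strongest reply has four parts.

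- **Visibility is inferred.** No sentence says that the fixation can be seen at the slit lamp. Group A's haptics are behind the iris and group B's flaps are of partial thickness. This stands, and it is why the conclusion is that masking cannot be relied on. A reader might infer that masking is simply absent for every slit-lamp outcome in every eye; the text does not establish that.
- **The primary outcomes can be masked.** Acuity, autorefraction and keratometry need no view of the fixation, and the Day 90 row of Table 1 has no separate lens-position item. This stands too. A reader might infer that the primary BCVA is unmasked, but that holds only if the examiner has seen the eye or the record, and no passage says so.
- **An article condenses the full protocol.** Who measures what, and in which order, is detail that may sit elsewhere. That answers a complaint about missing detail. It does not answer the point here: the article asserts masking without exception while naming methods that undercut it.
- **The trial is declared open-label.** A reader might go further and fault the decision not to mask patients, since the envelope is opened only during surgery. That decision is disclosed and consistent with the open-label label. Withholding the implant type from patients would be a different design choice, not the correction of an error.

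**Conclusion.** The masking statement is too broad as written. It cannot be relied on for IOL position, for centration and tilt, or for anterior-segment signs such as IOL decentration and pigment dispersion. All the outcome measures affected directly are secondary. Among the five listed postoperative complications, at least two are affected (decentration and pigment dispersion), and two are not affected by the nature of their measurement (raised intraocular pressure and cystoid macular edema).

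The conclusion rests on one inference: that the fixation, as Intervention Procedures describes it, is often recognizable to someone grading the lens. This may vary by eye.

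For BCVA the exposure is conditional, as set out above. It is tempting to put a number on possible observer bias in acuity. The documents support none: they give neither an SD for BCVA nor any size for such a bias, and observer behaviour distorts the comparison only to the extent that it differs between arms.

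Nothing here invalidates the trial. Its stated protection against detection bias is overstated for part of the outcome set, and it can be made firmer for the rest at little cost.

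**What to change.** 1. **Restate the claim, in the blinding section and in the Discussion.** Limit assessor masking to BCVA, autorefractometry and keratometry, and keep the statement that data analysts are masked. Say that outcomes graded by viewing the lens or its fixation are assessed without assured masking. Describe the NEI VFQ-25 as reported by unmasked patients.

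2. **Fix the order within visits.** At each visit where Table 1 already schedules them, take BCVA and refraction or keratometry before any slit-lamp examination. Use an examiner who has no access to the operative record, and ask patients not to disclose their procedure. To stay masked across visits, that examiner should not be the one who graded the same eye at the slit lamp earlier. This adds no assessment to Table 1.

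The cost is a less favourable masking claim and a fixed visit order, with the duties of acuity and slit-lamp examiners kept apart. Recruitment began in March 2025, so the visit order can change only the visits still to come. The wording can be corrected whatever the stage of the trial.
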